**Sample size calculation**

The adequate sample size for all objectives is calculated using openepi version 3 software. The sample size needed to estimate the utilization of MHS is calculated assuming the anticipated utilization of ANC (74%), births attended in an HF (48%), and PNC (34%) according to the report of 2019 Mini EDHS[[29](#_ENREF_29)], the margin of error of 5%, 95% confidence interval, 1.31 design effect. Based on the above information, the estimated sample size is 392 (ANC), 508 (births attended in a health facility), and 457 (PNC). The sample size needed for identifying the predictors associated with MHSU is calculated considering variables significantly associated with MHSU based on previous studies done in Northern Ethiopia [7], in rural Haramaya district, Eastern Ethiopia [10], and in Northwest Ethiopia [11]. For all calculations, power was set at 80%, level of confidence at 5%, and the ratio of unexposed-to-exposed were assumed to be 1. Hence, the sample size of 1,104 obtained from the second objective will be utilized due to it is the maximum sample size assessed and would be adequate to assess all objectives of this study. The minimum required sample size for the qualitative study will be determined according to the recommendation of Morse and Creswell for Phenomenological studies (20 in-depth interviews, 9 focus group discussions, and 20 key informant interviews) [[30](#_ENREF_30)]. The minimum required sample size for the third and fourth objectives is calculated based on the following considerations. Due to the lack of the previous cRCT on the same topic, assumptions on the proportion of women with knowledge on ODS in the control and intervention arms were taken from a previous quasi-experimental study. The proportion before the intervention was taken as the proportion in the control arm and the proportion after the intervention as the proportion in the intervention arm. Accordingly, P1 = 45.7% (proportion of women’s knowledge regarding ODS during pregnancy) in the control group, P2= 62.9% (proportion of women’s knowledge regarding ODS during pregnancy in the intervention arm) [[14](#_ENREF_14)], 95% CI, and 80% power. According to the above considerations, the estimated effective sample size for individual-based randomization is 286. For this objective, the sample size is adjusted to non-response rate (NRR) by dividing the initial sample size by the anticipated response rate. In case of knowledge regarding ODS during pregnancy, the adjusted sample size to NRR is 286/1 = 286.The minimum required number of clusters is computed by multiplying the effective sample size and ICC factors for both groups [28]. We received the typical value of ICC factor of 0.01 from range values (0.01 to 0.05) based on the existing recommendation [26]. Consequently, the minimum needed cluster number is 329*0.01 = 3.29 for both groups. Nevertheless, to maintain the sufficiency of the cluster and to have adequate power [26, 28], 12 clusters (*12 kebeles*) will be included in this study. To account for the effect of the cluster, the effective sample size is multiplied by a VIF of 1.26. The VIF is calculated with the assumption of an equal cluster size of 27 study subjects from 12 clusters (*kebeles*). Using ICC value of 0.01, (VIF = 1+ [(n-1) ICC]), where ‘n’ is the average cluster size [28]. Thus, the final estimated sample size is 360 (180 in the intervention arm and 180 in the control arm). However, the sample size calculated for the fourth objective which is designed to evaluate the effect of the intervention on MHSU is 1,126 (i.e., larger). Hence, the sample size of 1,126 obtained from the fourth objective will be utilized for this objective as well as it would be maximum or representatives of the sample for both objectives.

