**The measurements**

**ANC utilization** is measured as a proportion of women who utilized ANC from skilled providers (HEWs, midwives, nurses, health officers, and doctors) at least once during the last pregnancy using a woman's self-report. However, different studies considered different figures of ANC visits being optimum. For instance, some researchers had fixed 2 ANC visits to be adequate. The WHO suggests at least 8 ANC visits throughout pregnancy while the first visit will be conducted before 16 weeks or within the first trimester. Therefore, standardization of the numbers of ANC use is required to assist the comparison of diverse or different studies. Accordingly, we considered utilization of ANC as a woman who has at least one ANC follow-up which is similar to EDHS. Besides, the time must be within the first trimester or before 16 weeks of gestation. Moreover, women must consume more than 90 iron-folic acids (IFA) tablets or syrup, receive at least one dose of tetanus toxoid injection, have a laboratory test result of syphilis, and blood group.

**Institutional delivery utilization** is measured as the proportion of women who utilized institutions (governmental health centers or hospitals, and/or private hospitals or clinics) for delivery in their last pregnancy using a woman’s self-report.

**PNC utilization** is measured as the proportion of women who utilized a PNC visit within 42 days after giving birth at least once using a woman’s self-report.

**Maternal knowledge regarding ODS** will be measured using the 30 questions during three phases namely antepartum (9 questions), intrapartum (12 questions), and postpartum (9 questions). The correct answers are assigned a score of 1, while incorrect answers are assigned a score of 0. Lastly, the total knowledge scores range from 0 to 30. The study respondents who spontaneously mention at least 3 ODS during each phase are classified as having “good knowledge” and those who are not able to spontaneously mention 2 or fewer ODS have “poor knowledge”.

**Spontaneous knowledge** is defined as the knowledge of study participants who can name or call an ODS without being read the name of that sign by data collectors. Merely true ODS spontaneously mentioned by study participants will be recorded during the interview.

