**BPCR practice** will be measured using 5 components of the question as to whether or not the woman planned for her most recent pregnancy such as identified a closer proper HF for childbirth, founded and communicate an SBA, saved money, a material resource for childbirth, and other associated costs, prepared or arranged transportation to a proper HF in case of childbirth and obstetric emergency and identified and fixed the compatible blood group givers in case of blood requirements. If a woman prearranged at least three components out of 5, she will be considered as having “well prepared” and those who are prepared 2 or fewer considered “poorly prepared”.

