**Statistical data analysis**

Data will be entered into Epidata version 3.1 and exported to the Statistical Package for Social Science (SPSS) version 25 and Stata version 14 for further processing and analysis. During the analysis, all quantitative variables will be handled by recoding, calculations, and categorizations before carrying out the main analysis. Descriptive analyses will be carried out to get descriptive measures for the important variables of interest. The descriptive statistic techniques will be utilized for the data organization and presentation. All continuous data will be checked for the normal distribution. If approximately normal distributed the mean and SD will be reported. The missing data will be handled by using multiple imputation methods. The Principal Component Analysis (PCA) will be carried out for the computation of the wealth index. The effect of clustering will be checked by using an Intra-Cluster Correlation Coefficient (ICC) value. The multilevel analysis will be considered if the calculated value of ICC is greater than 5%. Before conducting a multilevel analysis, we will decide whether or not the multilevel model is required by doing a random intercept model. This model offers data regarding ICC which is utilized to determine whether a multilevel model is required or not. If the chi-square test is significant or the ICC value is greater than 5%, the multilevel analysis model is mandatory to consider. Both bi-variable and multivariable analyses using generalized mixed models with random effects will be carried out. The Generalized Estimated Equations (GEE) or multilevel regression models will be utilized to adjust for between and within-cluster variation for adjusted analysis. Those variables with p-values < 0.25 on the bi-variable analysis model will be included in a multivariable regression model to find out predictors independently associated with MHSU adjusting for other variables in the model. The candidate variables will be entered into the multivariable regression model using the ENTER regression method. The basic assumptions of generalized mixed models will be tested before proceeding with the analysis. The stratified and multivariable analyses will be used to control for the potential confounding variables. Effect modification will be examined using stratification and entering effect modifiers into the multivariable analysis model one at a moment. Multicollinearity among the independent variables will be also evaluated using a multiple linear regression model. The variance inflation factor (VIF) < 10 and tolerance statistics > 0.1 will be used to declare the absence of multicollinearity. The presence and strength of a statistically significant association between MHSU and the independent variables will be assessed using adjusted odds ratios (AORs) with a 95% CI. A statistically significant association between the variables of interest will be confirmed when the 95% CI of the AORs did not contain 1. All analyses of the study will be carried out using a 95% CI or 5% level of significance. Though, a statistical significance level will be adjusted to account for the effect of multiple comparisons problem using the Bonferroni corrections methods. The adjusted level of significance is computed by dividing the preset level of significance by the number of statistical tests conducted (outcome variables). In our case, the adjusted level of significance is 0.05/3 = 0.017. Thus, a statistically significant association will be declared when p-value less than 0.017. After the finish of the qualitative data collection, the tape-recorded data will be transcribed verbatim of the local language and translated to English. The coding and analysis of the qualitative data will be done using the thematic content analysis technique by Atlas-Ti software and presented in narratives. A paired t-test will be utilized to measure the mean change from baseline for both groups (intervention and control) groups. Then, an independent t-test will be utilized to compare the mean change of women’s knowledge regarding ODS and BPCR practice scores and MHSU for interventional groups against the mean change of the control group as effect size. To assess the effect of HEI on maternal knowledge regarding ODS and BPCR practice scores and MHSU, an intention-to-treat analysis will be done to compare outcomes between the two groups.

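### Objective 3 is sized on a pregnancy-phase knowledge proportion at 5% but tested on a mean score at 0.017, and the knowledge and preparedness categories have no stated role

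*Protocol*

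**What the plan says.** **Sizing.** The Sample size calculation section takes 45.7% for the control arm and 62.9% for the proportion with "knowledge regarding ODS during pregnancy in the intervention arm", with "95% CI, and 80% power". It concludes that "the estimated effective sample size for individual-based randomization is 286" and multiplies by a variance inflation factor of 1.26 to reach 360 ("180 in the intervention arm and 180 in the control arm"). It then adopts 1,126, the number from the service-utilization objective, for this objective too.

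**Definitions.** The measurements section builds a 0-30 total knowledge score from 9 antepartum, 12 intrapartum and 9 postpartum items. It also classifies women who name "at least 3 ODS during each phase are classified as having" good knowledge. For birth preparedness and complication readiness (BPCR) it lists five components and adds a cut-off: "If a woman prearranged at least three components out of 5, she will be considered as having" prepared well.

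**Tests.** The Summary assigns multilevel linear regression to knowledge and BPCR practice. The Statistical data analysis section compares, by independent t-test, the mean change in "knowledge regarding ODS and BPCR practice scores and MHSU for interventional groups against the mean change of the control group as effect size". It sets the significance level at 0.05/3 = 0.017, counting three outcome variables.

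**The concern.** Three forms of the knowledge outcome sit in one plan: a single-phase proportion (sized), a three-phase category (defined) and a 0-30 mean score (tested). BPCR has two, a score and a category. A reader who takes the 80% power as the power of the objective 3 test would be misled twice: it is for a different outcome, and for a 5% test rather than a 0.017 test.

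The categories add a second difficulty. They are formally defined but are neither assigned to the arm comparison nor excluded from it. The phrase about each phase does not settle whether a woman must reach three signs in all three phases or is classified separately in each. The definition of poor knowledge attaches a negation to the two-or-fewer threshold, so taken literally it is not the remainder after good knowledge. The Blinding section says neither the research team nor respondents can be masked, so which form supports a significance claim should be fixed in advance.

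**Working it through.** **1. Reproduce the plan's figure.** Inputs from the Sample size calculation section: p1 = 0.457, p2 = 0.629, power 80%, equal arms. Two-sided 5% is assumed from the 95% confidence level. With mean proportion 0.543 and difference d = 0.172:

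- n per arm = [1.960·√(2·0.543·0.457) + 0.842·√(0.457·0.543 + 0.629·0.371)]² / 0.172² = 130.5, so 131 (262 in total).
- With continuity correction: (n/4)·[1 + √(1 + 4/(n·d))]² = 141.9, so 142 (284 in total), against 286 stated.
- VIF = 1 + (27 − 1)·0.01 = 1.26, and 286 × 1.26 = 360.4, against 360 stated.

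The figure is therefore a two-proportion calculation at 5%. The protocol confirms the phase: "In case of knowledge regarding ODS during pregnancy, the adjusted sample size to NRR is 286/1 = 286". With 360 women and VIF 1.26, the same contrast without continuity correction has 83% power at 0.05 and 70% at 0.05/3.

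**2. Is the sized proportion the defined category?** On the per-phase reading, it corresponds to the antepartum category. On the all-phases reading it does not, except in one extreme case. Suppose, for illustration only, that every phase had the sized rates. Perfect concordance between phases leaves 45.7% against 62.9%; independence gives 0.457³ = 9.5% against 0.629³ = 24.9%. The protocol gives no rates for the other two phases.

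**3. Is the score the same contrast as the all-phases category?** No. A woman naming 9 + 12 + 2 signs scores 23 and is not good on all phases; one naming 3 + 3 + 3 scores 9 and is good.

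**4. What 1,126 women give.** Mean cluster size is 1,126/12 = 93.8. The design effect is 1 + (93.8 − 1)·ICC. The protocol cites an ICC range of 0.01 to 0.05 and uses 0.01. Score difference = (2.394 + 0.842)·√(2/effective n per arm), for 80% power at 0.05/3.

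| ICC | Design effect | Effective n per arm | Power, sized proportion, at 0.05/3 | Detectable score difference |
|---|---|---|---|---|
| 0.01 | 1.93 | 563/1.93 = 292 | 96-97% | 3.236·√(2/292) = 0.27 SD |
| 0.05 | 5.64 | 563/5.64 = 99.8 | 52-53% | 3.236·√(2/99.8) = 0.46 SD |

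Each power range covers the pooled and unpooled variance formulas. These are normal approximations; allowing for only 12 kebeles would lower the powers and raise the detectable differences somewhat. The standardised differences cannot be turned into score points or into power, because the protocol gives no score SD or expected score difference.

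**5. Illustration of what unlabelled categories could cost.** Suppose both categories were also tested at 0.05/3, making five tests (knowledge twice, BPCR twice, service utilization once), with correlation 0.8 between the two forms of each outcome. With no effect, the chance of at least one significant result is 6.2% at cross-outcome correlation 0.5 and 7.0% at 0. The protocol does not plan the category tests, and the correlations are assumed.

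**The case against.** The strongest reply is that the deciding form is already clear. Every between-arm test named for knowledge and BPCR is on the score: the Summary's linear model, the t-test of mean change, and the intention-to-treat sentence that again refers to scores. The study variables table defines both outcomes by their number of questions, without cut-offs. The adjusted odds ratios in the analysis section concern predictors of service utilization. This stands. A reader might infer that nothing in the protocol says which form carries the claim; the text does not support that. What is missing is a role for the categories and a link between the sized outcome and the tested one.

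A second reply is that 1,126 women, not 360, will be used. This also stands at the planned ICC. A reader might infer that objective 3 is underpowered; the protocol does not show that. The fall to 52-53% comes from the ICC rather than from the mismatch, and for the score no power figure can be derived either way.

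Third, a reader might infer that the error rate is inflated above 5%. That needs significance tests on the categories, which are not planned, so the 6.2-7.0% is only an illustration. It also counts service utilization as one test, although antenatal care, institutional delivery and postnatal care are measured separately.

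Finally, on the per-phase reading the sized proportion is one of the defined categories. That is fair, but it is still not the tested score, and the choice between readings is left open.

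Reporting details for category summaries could sit in a statistical analysis plan that is not at hand. The mismatch between sizing and test lies within the protocol itself.

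**Conclusion.** The point holds in a limited form. The power statement for objective 3 is attached to a pregnancy-phase proportion at 5%, while the planned tests use mean scores at 0.017. The categories have no stated role, an ambiguous phase rule and a poor class that is not worded as the complement of good. The score is the likely intended endpoint.

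The consequence is mainly one of clarity and of a misattributed power claim, not a demonstrated shortage of women. The size rests on the protocol's ICC range, equal clusters, 12 kebeles, a two-sided test and normal approximations. Under these, the sized proportion keeps about 96-97% power at ICC 0.01 and about 52-53% at ICC 0.05, and the score test can detect about 0.27 to 0.46 SD.

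**What to change.** **The measurements and Statistical data analysis.** State that the confirmatory contrasts are the arm differences in the 0-30 knowledge score and the 0-5 BPCR score, each tested at 0.017. Both should come from the multilevel linear model with kebele as cluster, as in the Summary, in place of the plain independent t-test. For these two contrasts the model should apply whatever the ICC screen described in the analysis section shows.

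**Categories.** State that good/poor knowledge, well/poorly prepared and the phase subscores are descriptive, without significance claims. Say whether good knowledge is judged per phase or across all phases, and define poor as everyone else.

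**Sample size calculation.** State that 286, 360 and 80% power apply only to the pregnancy-phase proportion at 5%. Add the score difference detectable with 1,126 women in 12 kebeles at 0.017: about 0.27 SD at ICC 0.01 to 0.46 SD at ICC 0.05, for 80% power.

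**Cost.** Wording only; the same items are collected from the same women. The categories lose any significance claim, and the power statement for objective 3 becomes qualified and less favourable.

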**Methods:** A community-based cross-sectional study will be carried out to assess the utilization and predictors of maternal health care. A phenomenological qualitative study will be conducted to explore perceptions, barriers, and facilitators of maternal health care. A cluster randomized controlled trial will be employed to assess the effect of health education on maternal knowledge about the obstetric danger signs, birth preparedness and complication readiness plan, and maternal health service utilization (MHSU). The minimum required sample size is 1,104 for a cross-sectional study. To explore perceptions, barriers, and facilitators of maternal health care a minimum of 20 in-depth interviews, 3 focus group discussions per group, and 20 key informative interviews will be conducted. The minimum required sample size to assess the effect of health education on outcomes is 1,126. A multi-stage sampling method will be used to select the study participants for a cross-sectional study. A maximum variance sampling method will be used for the qualitative study. A cluster-randomized sampling method will be utilized for the interventional study. Quantitative data will be collected using a validated, pre-tested, and structured questionnaire. Qualitative data will be collected using pre-tested focus group discussions, in-depth interviews, and key informant interviews guides until information saturation is reached. The intervention group will be received 12 rounds of pre-recorded audio-based health education. The utilization of maternal health care will be measured at baseline and 6 months after the intervention. Data will be entered into Epi Data version 3.1 and exported to the SPSS and Stata software for analysis. Descriptive analyses will be carried out to get descriptive measures for the important variables of interest. The generalized estimated equations analysis will be used to assess the potential predictors of MHSU. The coding and analysis of the qualitative data will be done using the thematic content analysis technique by Atlas-Ti software and presented in narratives. For maternal knowledge about the danger signs and practice of birth preparedness and complication readiness, the multilevel linear regression models will be utilized. The intention-to-treat analysis will be used to compare outcomes between groups. Paired and independent t-tests will be used to compare the effect of an intervention. Statistical significance level will be adjusted to account for the effect of multiple comparisons problems using the Bonferroni corrections methods.

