**The inclusion and exclusion criteria**

All systematically selected WRA who gave live birth in the last 12 months, all purposely selected service providers and users, all pregnant mothers residing in the selected *kebeles* for at least for 6 months and have no plan to change residence during the implementation of an intervention, no psychiatric problems, capable of providing written informed consent, and voluntary to be visited by WDT facilitators, data collectors, and supervisors will be included for this study. Women who have a severe illness during the data collection period will be excluded from this study due to unable to communicate. Also, study subject who have a psychiatric disorder will be excluded due to that could affect participation and consent procedure. Similarly, women who experienced stillbirth and infant deaths will be excluded because the questions from this study are expected to re-memorize women the unfavorable pregnancy outcome they had faced. This may seriously affect maternal participation and genuine response. Midwives who have been serving in the maternal and child health case team for less than two years will be excluded. Due to this reason, these midwives have less experience and interaction with pregnant women and couldn’t provide in-depth information on perceptions, barriers, and facilitators of MHSU. Moreover, all WRA included in the quantitative study will be excluded because they have information during the quantitative study that may introduce information bias.

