**Intervention procedure**

WDA volunteers will be recruited by using the following selection criteria as able to read and write the Sidama language and are willing to do the intervention. Following recruitment, intensive training will be given for 1 week on the topics. One health education session consists of key messages on normal pregnancy, danger signs and complications during pregnancy, delivery, and the postpartum period, the practice of birth preparedness as well as complication readiness, and the benefits of MHSU. The other actions executed by WDA facilitators will be the motivating mother and their families for MHSU. One hour will be allocated for each session, from this 20 minutes will be allowed for the lecture which is moralistic in nature and the remaining 40 minutes will be allowed for raising questions and responses. After the session, some of the women will be selected to carry out role play which is basic to demonstrate the important messages and share experiences. This will be done to repeat the information provided to enable them to internalize the key message. The women will be also exposed to posters to reinforce the session message. The session will be conducted 2 times per month for six months. The follow-up will be conducted every month or more repeatedly if any potential problems indicated.

Interventional group (n= 563)

Control group (n= 563)

Included in to study (n = 1,126)

Randomization

Received CLHEI (n= 563)

Loss to follow up (n=)

Loss to follow-up (n=)

Analyzed at 6 months (n=)

Received routine intervention (n= 563)

Analyzed at 6 months (n=)

**Figure 1:** Flow Diagram for randomization of study participants in to intervention and control groups in Dale and Wonsho districts of Sidama region, Ethiopia.

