**The study variables**

| Outcome variables | Definition |
| --- | --- |
| MHSU | Utilization of maternal health care measured using the yes or no questions at the baseline and after 6 months of intervention. |
| Knowledge of obstetrics danger signs | Will be measured by using the 30 knowledge assessment questions. |
| Birth preparedness and complication readiness practice | Will be assessed using the 5 practice assessment questions. |
| Perceptions, barriers, and facilitators | Perceptions, barriers, and facilitators of MHSU that affect the utilization of MHS will be explored qualitatively. |
| Exposure variable | Definition |
| Health education | **Intervention group:** will receive routine plus pre-recorded audio-based HEI package for six months until date of delivery.  **Comparator group:** will receive the routine health education package for six months until the date of delivery as per the Ethiopian guidelines. |
| Predictors | Predictors that predict the utilization of MHS. It will be measured retrospectively. Socio-economic and demographic, obstetric characteristics, health facility and socio-cultural related predictors. |
| Covariates | Place of residence (urban/rural), educational status of women and her spouse, wealth index, maternal age, occupational status of women and her spouse |

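### The birth-preparedness item refers to the most recent pregnancy, so in women pregnant at baseline the change score can compare two different pregnancies, and its timing relative to birth is not fixed

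*Protocol*

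**What the plan says.** - **Outcome.** The measurements section defines BPCR practice once, with no separate wording for baseline and follow-up. It records "whether or not the woman planned for her most recent pregnancy such as identified a closer proper HF for childbirth", together with four further arrangements. Scoring is by count: "If a woman prearranged at least three components out of 5, she will be considered as having" prepared well; two or fewer counts as poorly prepared.
- **Participants.** The inclusion and exclusion criteria admit to the trial "all pregnant mothers residing in the selected *kebeles* for at least for 6 months". No gestational-age window or parity criterion is given.
- **Analysis.** Statistical data analysis states: "A paired t-test will be utilized to measure the mean change from baseline for both groups (intervention and control) groups". An independent t-test then compares mean change between the arms, for BPCR among other outcomes, and this contrast is named as the effect size. The analysis is by intention to treat.
- **Intervention period.** The study variables table says the intervention arm "will receive routine plus pre-recorded audio-based HEI package for six months until date of delivery". Intervention procedure adds: "The session will be conducted 2 times per month for six months".
- **Follow-up time.** It is stated for maternal health service utilization only. The Summary counts six months from the intervention; the study variables table counts six months under the intervention. Figure 1 shows one analysis point, at six months. BPCR has no follow-up time of its own.
- **Masking.** Under Blinding, neither the research team nor the respondents are masked.

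**The concern.** A change score is meaningful only if both measurements refer to the same thing. For a woman who is already pregnant when first interviewed, the most recent pregnancy can mean the current one, for which she may have arranged little so far, or her last completed one, for which any plan is finished. Nothing in the definition chooses between them. BPCR is an outcome of Paper III and stands in the trial hypothesis, so the ambiguity reaches a main result. It also cannot be repaired at the analysis stage: once the question has been asked this way, the pregnancy each woman had in mind cannot be recovered.

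A second weakness lies at follow-up. If BPCR is asked after the birth, an unmasked woman recalls her plan knowing where she delivered. Items such as having identified a facility or arranged transport are open to colouring by that knowledge. Since the intervention aims to raise facility delivery, such colouring could differ between the arms.

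**Working it through.** **1. Length of the intervention.** The Summary says "The intervention group will be received 12 rounds of pre-recorded audio-based health education". Two sessions per month × 6 months = 12, so the stated figure is reproduced and the intervention lasts six months, about 26 weeks.

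**2. Which pregnancy each answer refers to.**

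| Woman | Baseline answer | Follow-up answer (after birth) |
|---|---|---|
| First pregnancy | index pregnancy, plan in progress | index pregnancy |
| Earlier birth, reads the item as the current pregnancy | index pregnancy, plan in progress | index pregnancy |
| Earlier birth, reads the item as the last completed pregnancy | earlier pregnancy, plan finished | index pregnancy |

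The third row compares two pregnancies. The first two rows compare two stages of one pregnancy.

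**3. Effect on the two analyses.** Let π be the share of women whose baseline answer concerns an earlier pregnancy, P the mean score for that earlier pregnancy, C the mean baseline score for the current one, and F the mean follow-up score. The documents give none of these values; only the structure matters here.

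- Mean baseline = πP + (1 − π)C.
- Within-arm mean change = F − C − π(P − C). The last term is due to the wording alone and vanishes only if π = 0 or P = C.
- Between-arm difference in mean change = F(intervention) − F(control), if π, P and C have the same expectation in both arms. The wording term cancels.
- The variance of the baseline score gains the term π(1 − π)(P − C)², which adds noise to the change score.

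So the paired test is distorted, while the randomised contrast mainly loses precision.

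**4. Share of women already delivered at follow-up.** Assumptions, none of them in the protocol: birth at 40 weeks, and gestation at enrolment uniform from a to b weeks.

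*Summary wording, counted from the end of a six-month intervention:* 26 + 26 = 52 weeks after baseline. This exceeds 40, so all women have delivered whatever their gestation at entry.

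*Variables-table wording, 26 weeks after baseline:* a woman has delivered only if she entered after 40 − 26 = 14 weeks. Share = (b − max(a, 14)) / (b − a), taken as 0 if b ≤ 14.

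| Enrolment window (weeks) | Calculation | Delivered |
|---|---|---|
| 6–14 | 0/8 | 0% |
| 8–16 | 2/8 | 25% |
| 8–20 | 6/12 | 50% |
| 8–24 | 10/16 | 62.5% |
| 0–40 | 26/40 | 65% |
| 8–28 | 14/20 | 70% |
| 8–36 | 22/28 | 79% |
| 12–40 | 26/28 | 93% |
| 14–28 | 14/14 | 100% |

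A full six months of sessions before birth requires entry by about 14 weeks. Under the variables-table wording, almost no such woman would have delivered at follow-up, so institutional delivery and postnatal care could not be measured in her. The stage at which BPCR is asked is therefore undetermined, and the timing statements do not fit together.

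**The case against.** The strongest reply is that, for a pregnant woman, the most recent pregnancy is most naturally the current one. The text is an operational definition rather than the questionnaire, and the tools are to be back-translated and pre-tested. Moreover, the named effect size is the between-arm contrast, on which an ambiguity common to both arms has no systematic effect.

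Much of this stands. The ambiguity is no evidence of bias in the randomised comparison; step 3 shows that it cancels in expectation. But it leaves the paired within-arm test uninterpretable and costs precision. With 12 clusters, balance between the arms in parity is not assured either. Pre-testing may reveal the problem, but the protocol fixes no answer to it.

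A reader might infer three stronger points, which the documents do not support:

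- **Most women report their plan after the birth.** This holds for all women if follow-up is counted from the end of the intervention. Under the other wording it depends on gestation at entry, which is not stated. Early entry is plausible, since the package is described as lasting six months up to delivery. The delivery and postnatal outcomes suggest an interview after birth, but none is specified for BPCR.
- **Women still pregnant are scored as poorly prepared.** They are not, by default. The score counts arrangements, and a pregnant woman with three or more is well prepared.
- **BPCR and place of delivery are recorded in the same interview.** This is only inferred; neither the BPCR interview time nor the question order is given.

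Nor does reporting after the birth contradict the definition, which asks in the past tense what was arranged. The issue there is recall.

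**Conclusion.** The point holds in a limited form. The reference pregnancy for BPCR is not fixed for women who are pregnant at baseline, although change from baseline is analysed. For women with an earlier birth, the change can span two pregnancies. The within-arm paired result is shifted by π(P − C), whose size the documents do not allow to be estimated. The between-arm contrast gains noise and is not necessarily biased, provided that the baseline question is put in the same way in both arms.

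The timing of BPCR relative to birth is also open: all women delivered under one wording, and anywhere from 0% to 100% under the other, depending on the assumed enrolment window. Colouring of recall by the place of delivery is a possibility where BPCR is asked after birth, not an established bias. The matter deserves correction because the change is nearly free before data collection and impossible afterwards.

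**What to change.** 1. In The measurements, for the trial, replace the reference to the most recent pregnancy with *the current (index) pregnancy* at both assessments.
2. At follow-up, ask what was arranged before labour began, and put these items before the place-of-delivery questions.
3. Reconcile the follow-up timing in the Summary and in the study variables table, so that BPCR has one stated follow-up time relative to birth for all women.
4. Keep all randomised women in the analysis. Scoring only those who have delivered would conflict with the planned intention-to-treat analysis.
5. In Statistical data analysis, state that the conclusion on BPCR rests on the between-arm comparison. Even with the index pregnancy named, baseline and follow-up fall at different stages of it, and preparation can be expected to increase as birth approaches, so the within-arm paired test should be descriptive at most.

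The cost is a small change to questionnaire wording and order, and to the protocol text, before data collection starts.
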